## 2、 Statistical Analysis Plan

### Data set

After the electronic database was locked, the database was divided into Intention-to-Treat analysis (ITT), Per Protocol analysis (PP), and Safety Set (SS) using the following criteria.

**Intention-to-treat (ITT)** refers to all participants who were randomized into different treatment groups, regardless of whether they completed the treatment as assigned or not.

**Per protocol (PP)** refers to the set of cases that meet the inclusion criteria, do not meet the exclusion criteria, and have completed the treatment protocol. Each subject in the PP dataset is a valid case or sample with good adherence, no protocol violations, and complete baseline values for key indicators. Prespecified sensitivity analyses were conducted using complete-case data.

**Safety set (SS)** refers to the actual data for subjects who receive at least one intervention after randomization and for whom safety indicators are documented. The incidence of adverse reactions is calculated using the number of cases in the safety set.

**Adverse events:** Will be analyzed, with the number of cases, category, and severity of occurrences counted separately and their relationship to the intervention.

### Covariates and subgroup analysis

If there are statistically significant differences in the inter-group comparison of baseline indicators, covariates should be included in the analysis after intervention for correction. Use Generalized Estimating Equation (GEE) model to analyze primary and secondary outcome measurements. While including baseline measurements and IPAQ as covariates in the analysis. In addition, subgroup analysis will be performed by sex, age, education, BMI at baseline, GDS-15. The subgroup analysis will be carried out as exploratory.

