### Study Design

This study is a randomized, double-blind, placebo-controlled clinical trial conducted in China between October 2022 and February 2024. Eligible participants will be randomly assigned to two groups: (1) The experimental group (Tai Chi Chuan + 1-Hz rTMS), and (2) The Sham group (Tai Chi Chuan + Sham-rTMS). The flowchart of this trial is shown in **Figure 1**.

Assessments will be conducted at the following time points: Screening/Baseline (T1): Conducted two weeks prior to the start of the study/intervention. Intervention (T2): Conducted immediately after the completion of the 6-week intervention. Follow-up (T3): Conducted at 12 weeks after the end of the intervention. At screening, inclusion and exclusion criteria, as well as diagnostic criteria (**Table 1**), will be assessed, and demographic information (such as age, gender, education, medication history in the past two weeks, comorbid, tea, alcohol consumption, and smoking status) will be collected. Cognitive and sleep outcomes will be evaluated at baseline, post-intervention, and follow-up, and objective sleep parameter will be collected using objective wristwatches before and after the intervention. Within 6 weeks after the end of the intervention, the International Physical Activity Questionnaire (IPAQ) will be used to record the exercise status of all participants to monitor the frequency and intensity of exercise throughout the study period.

**Table 1** Schedule of assessments

| Visits                                                     | Study initiation                            |                                             |                            |
|------------------------------------------------------------|---------------------------------------------|---------------------------------------------|----------------------------|
|                                                            | Enrolment/
Baseline
T1
week-2-(-1) | Intervention a
T2
week 1-6 | Follow-up
T3
week 12 |
| Demographics                                        |                                             |                                             |                            |
| Clinical diagnosis of primary insomnia following the DSM-5 | X                                           |                                             |                            |

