| International Physical Activity Questionnaire b |   |   | X |

a This visit will also take place if the patient withdraws from study or is terminated early

b The International Physical Activity Questionnaire will be administered weekly after the intervention

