### Data management and general analysis

A comparison of baseline characteristics of the selected subjects in the two groups was conducted to assess comparability. Intervention effect evaluation included determining

intervention effect indicators and comparing intervention effects between groups. The primary outcome evaluation used the ITT dataset as the main dataset for intervention effect evaluation and the PP dataset for sensitivity analysis. Secondary outcome indicators were evaluated using the PP dataset. Safety assessment included statistical analysis of adverse events such as dizziness and falls, with the SS dataset used for safety assessment.

All statistical analyses were performed using SPSS 24.0 software. Two-tailed tests were used for statistical analysis, the primary outcome indicator is  $P < 0.025$  and the secondary outcome indicator is  $P < 0.05$  are considered statistically significant in comparison between groups. Continuous data were presented as means, standard deviations, or medians, and interquartile ranges depending on the normality of distribution. Categorical data were presented as frequencies (percentages). Normality tests were conducted for variable distributions, and independent sample t-tests were used for intergroup comparisons of normally distributed continuous data. Non-parametric tests were used for statistical analysis of non-normally distributed continuous data. Chi-square tests were used for comparisons of categorical variables, with the Fisher exact probability test used when necessary.

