### **Analysis of primary endpoint**

Statistical analysis of the primary outcome indicators was conducted using the ITT dataset and the PP dataset. The baseline measurements of the study subjects were adjusted using GEE model to compare the intervention effects in each group. At a single time point, the intergroup differences at baseline, 6-week postintervention, and during 12-week follow-up are compared using independent sample t-tests or Mann-Whitney U tests.

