### **Analysis of secondary endpoints**

Statistical analysis of the secondary outcome indicators was performed using the PP dataset. The baseline measurements of the study subjects were adjusted using a generalized estimating equation model to compare the intervention effects in each group. At a single time point, the intergroup differences at baseline, 6-week postintervention, and during 12-week follow-up are compared using independent sample t-tests or Mann-Whitney U tests.

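### Beyond the baseline measurements and IPAQ, covariates enter the GEE models only if their baseline difference is statistically significant, so chance imbalance rather than prognostic value completes the model

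*Combined protocol and SAP*

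**What the plan says.** The SAP section on covariates and subgroup analysis contains two instructions about adjustment.

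- The first is conditional: "If there are statistically significant differences in the inter-group comparison of baseline indicators, covariates should be included in the analysis after intervention for correction". It gives no list of candidate indicators, no significance threshold for the baseline tests and no limit on how many covariates may enter.
- The second has no condition. It follows the choice of GEE for primary and secondary outcomes: "While including baseline measurements and IPAQ as covariates in the analysis". The primary endpoint section repeats the baseline adjustment ("The baseline measurements of the study subjects were adjusted using GEE model to compare the intervention effects in each group"), and so does the secondary endpoint section ("The baseline measurements of the study subjects were adjusted using a generalized estimating equation model").

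Baseline comparisons that could feed the conditional rule are planned in two places. The general analysis section says "A comparison of baseline characteristics of the selected subjects in the two groups was conducted to assess comparability". The endpoint sections test the outcomes themselves: "the intergroup differences at baseline, 6-week postintervention, and during 12-week follow-up are compared using independent sample t-tests or Mann-Whitney U tests".

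The protocol's Study Design section lists the demographic and lifestyle items collected at screening: "age, gender, education, medication history in the past two weeks, comorbid, tea, alcohol consumption, and smoking status". In the SAP, age, sex and education appear only as subgroup factors, not as fixed covariates. The randomisation section describes 1:1 allocation in blocks of four and names no stratification factor.

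**The concern.** Under correct randomisation every baseline difference between the arms is due to chance. A P value for that difference tests a hypothesis already known to be true. It does not show whether the variable predicts the outcome, which is what makes a covariate worth adjusting for. The rule can therefore admit an irrelevant variable that happens to be imbalanced and leave out a prognostic one that happens to balance.

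Education is the clearest case. The protocol's own MoCA scoring adds a point for 12 years of education or less, so the plan accepts that education affects this primary outcome. Yet education enters the MoCA model only if the arms happen to differ on it significantly.

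Two things are at stake: whether the covariate set for the two primary outcomes can be written down before the data are seen, and how much precision is given up.

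**Working it through.** **Inputs from the documents.** PSQI 11.26 (SD 1.52) against 12.48 (SD 2.59), alpha 0.05, power 0.80, at least 49 per group, 55 after 10% dropout, 110 in total (Sample size). Two-sided tests, primary outcomes at P < 0.025 (Data management and general analysis). Eight demographic and lifestyle items (Study Design).

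**Assumptions, not in the documents.** A 0.05 threshold for the baseline tests, independence of those tests, and every correlation used below.

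**1. The plan's own figure.** Pooled SD = √((1.52² + 2.59²)/2) = 2.123, and d = 1.22/2.123 = 0.575. With the noncentral t, two-sided alpha 0.05 and 49 per group, power is 0.804. 49/0.9 = 54.4, rounded up to 55 per group, 110 in total. The stated sample size reproduces. The point does not dispute it.

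**2. How often the rule omits a given predictor.** Under randomisation a baseline test at 0.05 is significant 5% of the time. A given covariate is therefore omitted 1 − 0.05 = 95% of the time, however strongly it predicts the outcome.

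**3. How often the rule changes the model by chance.** For k independent tests, P(at least one significant) = 1 − 0.95^k. For the eight listed items, 1 − 0.95⁸ = 1 − 0.663 = 0.337, about 34%.

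**4. What the omission costs.** The comparator must already contain the outcome's own baseline value, because the plan includes it. If that value has correlation r with the outcome, and the further covariates have partial correlation R given it, the effective standardised effect is d/√((1 − r²)(1 − R²)). Power at 49 per group, two-sided alpha 0.025 (single time point, t approximation with 96 degrees of freedom):

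| Baseline r | R = 0 | R = 0.1 | R = 0.2 | R = 0.3 |
|---|---|---|---|---|
| 0.4 | 0.794 | 0.798 | 0.812 | 0.834 |
| 0.5 | 0.841 | 0.845 | 0.857 | 0.876 |

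The gain from fixing the further covariates runs from 0.4 points (0.798 − 0.794) to 4.0 points (0.834 − 0.794). The rule forgoes nearly all of it, since it admits a given covariate only about 5% of the time. These inputs are for PSQI. The documents give none for MoCA.

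**5. Type I error under the rule.** Simulation used 55 per arm, nominal 0.025, and one continuous covariate adjusted for only if its baseline P was below 0.05. Rejection rates under no effect were 0.025, 0.022 and 0.016 for covariate–outcome correlations of 0.3, 0.5 and 0.7 (8,000 replicates; simulation standard error √(0.025 × 0.975/8,000) ≈ 0.002). With the outcome's baseline always in the model and 8 or 18 independent candidates screened at 0.05, the rates lay between 0.021 and 0.027. The rule is neutral to slightly conservative.

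**The case against.** The strongest reply is that the most important covariate is already fixed. Baseline measurements are most naturally read as each outcome's own baseline value, usually its best predictor, and they enter without any test. This stands, and it rules out several stronger readings.

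- **That all adjustment covariates are chosen by significance.** Only those beyond the baseline measurements and IPAQ are.
- **That fixed adjustment would raise power from 0.71 to as much as 0.84.** At d = 0.575, 49 per group and alpha 0.025, power is 0.714 with no covariate and 0.841 with a multiple correlation of 0.5. But 0.714 belongs to an unadjusted comparison, which is not the planned GEE. Most of that gain is probably already in the plan.
- **That a spurious trigger has a 60% to 71% chance.** Those figures follow from 18 or 24 independent tests (1 − 0.95¹⁸ = 0.603; 1 − 0.95²⁴ = 0.708). The counts include outcome baselines, 9 of the 18 and 15 of the 24, each already in the model for its own outcome. Many of the scales also overlap, so independence is doubtful.
- **That the error rate is inflated.** The simulations show no inflation.
- **That the model can be steered after seeing results.** The trigger is baseline data, not outcomes, and the randomisation section gives the statistician only group codes until the analysis is complete.

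What the reply does not remove is the conditional sentence. If baseline measurements means the outcome's own baseline, every other covariate still depends on chance imbalance. If it means all baseline variables, the conditional sentence is redundant and the two instructions conflict. On neither reading is the covariate set settled.

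**Conclusion.** The point holds for the further covariates only. The rule selects on chance imbalance and ignores prognostic value. It also leaves the final covariate set for the primary and secondary GEE models unknown until the data are seen. A given predictor is omitted about 95% of the time, and at least one of the eight listed items enters by chance about 34% of the time. Both figures assume a 0.05 threshold, and the second also assumes independent tests.

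The loss of precision is modest: about 0.4 to 4 power points for partial correlations of 0.1 to 0.3 on top of a baseline correlation of 0.4 to 0.5, all assumed. A reader might infer that the primary P values are invalid; the documents and the calculations do not support that. This is a free improvement to prespecification and precision, worth making for that reason.

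**What to change.** In the SAP section on covariates and subgroup analysis, delete the sentence that makes adjustment depend on significant baseline differences. Replace it with one covariate set for every primary and secondary GEE model: the outcome's own baseline value, age, sex and years of education. State that baseline measurements means the baseline value of the outcome being analysed. Fix this before the first unblinding, because the present rule can only be applied once group codes are released. Label any adjustment for an observed imbalance as a sensitivity analysis.

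Whether IPAQ should stay is a separate question: by the footnote to the assessment schedule, "The International Physical Activity Questionnaire will be administered weekly after the intervention", so it is a post-randomisation variable.

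The cost is SAP wording only. Age, sex and education are already collected at screening, and the MoCA scoring rule already turns on years of education. The sample size does not change.

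### The covariate section puts IPAQ, which is recorded only after treatment, into the GEE; that model does not target the total rTMS effect, and the endpoint sections describe a different model

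*Combined protocol and SAP*

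**What the plan says.** The SAP section on covariates and subgroup analysis gives one model for all efficacy outcomes: "Use Generalized Estimating Equation (GEE) model to analyze primary and secondary outcome measurements". It then adds: "While including baseline measurements and IPAQ as covariates in the analysis".

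The protocol places IPAQ after treatment. Study Design states: "Within 6 weeks after the end of the intervention, the International Physical Activity Questionnaire (IPAQ) will be used to record the exercise status". Table 1 ticks IPAQ only under T3, and footnote b reads: "The International Physical Activity Questionnaire will be administered weekly after the intervention". The stated purpose is "to monitor the frequency and intensity of exercise throughout the study period", yet no collection point is listed at baseline or during treatment. The T2 assessment is "Conducted immediately after the completion of the 6-week intervention".

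The endpoint sections describe the GEE without IPAQ. For the primary outcomes: "The baseline measurements of the study subjects were adjusted using GEE model to compare the intervention effects in each group". For the secondary outcomes: "The baseline measurements of the study subjects were adjusted using a generalized estimating equation model to compare the intervention effects in each group". Both sections also plan two-group tests without covariates (t-test or Mann-Whitney U) at each visit.

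The SAP gives no reason for adjusting for IPAQ, no rule for turning weekly records into one covariate, and no explicit plan for a GEE without IPAQ should the covariate section govern.

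**The concern.** Randomisation balances what precedes it. A variable recorded after treatment can itself be changed by treatment, and conditioning on it changes the question. The IPAQ-adjusted coefficient compares arms at equal later activity, which is not the total effect of adding active rather than sham rTMS to Tai Chi.

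Distortion can arise in three ways:

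- If rTMS changes activity and activity affects sleep or cognition at T3, adjustment takes that part of the effect out.
- If a better T2 result leads to more activity, adjusting the T2 outcome for IPAQ means adjusting it for its own consequence.
- If rTMS changes activity and an unmeasured factor drives both activity and outcome, adjustment induces an association between arm and outcome that treatment did not cause.

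At stake is the interpretation of the PSQI and MoCA results from the GEE. The choice between two candidate models is also left open.

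**Working it through.** **Timing.** Baseline (T1) precedes treatment and has no IPAQ. T2 comes at the end of treatment, before any IPAQ record. T3 is given as 12 weeks after the intervention in the text and as week 12 in Table 1; on either reading IPAQ follows T2. So IPAQ is post-randomisation throughout. It cannot cause the T2 outcome, but it can be a consequence of it or share causes with it.

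**The plan's own effect size (Sample size section).** PSQI 11.26 (SD 1.52) versus 12.48 (SD 2.59).

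- Difference = 12.48 - 11.26 = 1.22 points.
- Pooled SD = sqrt((1.52² + 2.59²)/2) = sqrt(4.509) = 2.123.
- d = 1.22/2.123 = 0.575.
- Two-sided alpha 0.05, power 0.80: the noncentral t calculation gives 49 per group (power 0.804), as stated. Then 49/0.9 = 54.4, so 55 per group and 110 in total, also as stated.

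This calculation does not involve IPAQ, so the point leaves the sample size unchanged. It supplies only a scale.

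**Illustration for T3.** The links are assumptions. Let a be the rTMS effect on IPAQ (SD) and b the IPAQ effect on T3 PSQI (SD per SD). In a linear model with IPAQ as a pure mediator, adjusted effect = total effect - a × b. Taking the total as a 0.57 SD reduction:

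- a = 0.2, b = -0.2: 0.04/0.57 = 7% removed.
- a = 0.5, b = -0.3: 0.15/0.57 = 26% removed.

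**Simulation at trial size.** 49 per arm, total effect -1.22 points, assumed baseline coefficient 0.5, two-sided alpha 0.025, 4,000 runs per scenario. A linear model was fitted at each visit, with the baseline value only and then with IPAQ added.

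| Assumed scenario | Visit | Baseline only: estimate (power) | IPAQ added: estimate (power) |
|---|---|---|---|
| rTMS does not affect IPAQ; IPAQ prognostic (b = -0.3) | T3 | -1.22 (0.84) | -1.22 (0.89) |
| a = 0.3, b = -0.3 | T3 | -1.21 (0.83) | -1.01 (0.71) |
| a = 0.5, b = -0.4 | T3 | -1.22 (0.83) | -0.79 (0.51) |
| a = -0.3, b = -0.3 | T3 | -1.22 (0.83) | -1.40 (0.95) |
| Better T2 PSQI raises activity, 0.2 SD per SD | T2 | -1.22 (0.84) | -1.19 (0.82) |
| Better T2 PSQI raises activity, 0.4 SD per SD | T2 | -1.22 (0.84) | -1.07 (0.77) |

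From the unrounded estimates, the T2 attenuation is (1.223 - 1.186)/1.223 = 3% and (1.221 - 1.066)/1.221 = 13%. A direct effect of rTMS on later activity, with no shared cause, left T2 unchanged at -1.22.

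**No true PSQI effect.** With a = 0.3 and an unmeasured shared cause (loading 0.5), adjustment produced a false difference of 0.16 to 0.17 points and a type I error of 0.037 to 0.043 against 0.025. When rTMS affected neither activity nor PSQI, type I error was 0.025 to 0.029 even with a shared cause.

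**Limit.** These are separate fits by visit. A GEE with one IPAQ coefficient across both visits would mix the T2 and T3 mechanisms, and the SAP does not say which form is meant.

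**The case against.** The strongest reply is that bias is not shown. It needs rTMS to change later activity, and the documents contain no evidence that it does. Both arms receive the same Tai Chi programme and participants are meant to be blinded to coil type, which limits behaviour change from knowing the allocation. Without that link adjustment is harmless, and it can gain power (0.89 against 0.84 above). This stands: a reader might infer that the rTMS estimate is biased, and the documents support only that it may be.

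A reader might also infer that every efficacy analysis is affected. The documents do not support that. The endpoint sections name only baseline adjustment, and they plan unadjusted tests at each visit, which for the primary outcomes include the ITT set. Nor does IPAQ cost the secondary outcomes an ITT status, since they are analysed in the PP set anyway.

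A third inference would be that the effect is bound to shrink. That holds only for the assumed positive link from rTMS to activity; a negative link moves the estimate away from zero. At the low end the loss is 0.2 × 0.2 = 0.04 SD, small beside a standard error of about sqrt(2/49) = 0.20 SD. The mediator calculation also does not apply to T2.

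The reply does not remove the timing problem. The covariate section expressly covers primary and secondary outcomes, and the endpoint sections do not exclude IPAQ. Whether rTMS alters activity cannot be known in advance, so the confirmatory model should not depend on it.

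**Conclusion.** The point holds in conditional form. As written in the covariate section, the GEE adjusts for a variable that exists only after treatment and, for T2, only after the outcome. That model does not target the total effect of active versus sham rTMS. It is unbiased for that effect if rTMS leaves activity unchanged, and may be biased in either direction if it does not.

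The size cannot be derived from the documents. The ranges of about 7% to 26% at T3 and 3% to 13% at T2 are illustrations under assumed links, not estimates for this trial.

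The inconsistency needs no such assumption: the covariate section and the two endpoint sections describe different covariate sets for the same GEE.

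**What to change.** Delete IPAQ from the GEE models for primary and secondary outcomes. Adjust only for the baseline value of the outcome and other variables fixed before randomisation, and give the same covariate list in the covariate section and both endpoint sections. Report IPAQ by arm descriptively, or use it in an analysis labelled exploratory with a stated rule for summarising the weekly records.

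This costs about one sentence in the covariate section and a matching edit in the other two. No new data are needed and the sample size does not change. The downside is a small possible loss of precision if IPAQ is prognostic and unaffected by rTMS; in the first scenario of the table, power was 0.84 rather than 0.89.
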